## Abstract

**Background:**

The management of cognitive impairment is an important goal in the treatment of multiple sclerosis (MS). While cognitive rehabilitation has been proven to be effective in improving cognitive performance in MS, research in the elderly indicates a higher effectiveness of combined cognitive-motor rehabilitation. Here, we present the protocol of a randomised controlled clinical trial to assess whether a combined cognitive-motor telerehabilitation programme is more effective in improving working memory than only cognitive or motor training.

**Methods/design:**

The CoMoTeMS-trial is a two-centre, randomised, controlled and blinded clinical trial. A total of 90 patients with MS will receive 12 weeks of either a combined cognitive-motor telerehabilitation programme or only cognitive or motor training. The primary outcome is a change in the digit span backwards. Secondary outcomes are other cognitive changes (Brief International Cognitive Assessment for Multiple Sclerosis and Backward Corsi), Expanded Disability Status Scale (EDSS), 6-Min Walk Test, 25-Foot Walk Test, 9-Hole Peg Test, anxiety and depression, fatigue, quality of life, cognitive and physical activity level, electroencephalography and magnetic resonance imaging of the brain.

**Discussion:**

We hypothesise that the improvement in digit span backwards after 12 weeks of treatment will be significantly higher in the group treated with the combined cognitive-motor telerehabilitation programme, compared to the groups receiving only cognitive and only motor training.

**Trial registration:**

ClinicalTrials.gov NCT05355389. Registered on 2 May 2022.

**Supplementary Information:**

The online version contains supplementary material available at 10.1186/s13063-022-06697-9.

## Introduction

Multiple sclerosis (MS) is the most common inflammatory and neurodegenerative disease in young adults, affecting more than two million people worldwide [1], and between 34 and 65% of the persons with multiple sclerosis (PwMS) suffer from cognitive impairment (CI) [2]. CI in MS has a substantial, often detrimental effect on numerous aspects of daily life [3–5]. Its management is an important gap in the treatment of MS [6]. Cognitive rehabilitation is the most promising treatment strategy [6], with recent meta-analyses finding conclusive evidence that both cognitive rehabilitation interventions in general and memory rehabilitation improve objective cognitive performance [7–9]. However, many challenges remain that hamper implementation into daily practice; studies with larger sample sizes, inclusion of patients with progressive disease, assessment of the effects on daily life and long-term follow-up data are still lacking [6].

The link between CI and physical performance is of particular interest. Studies have found numerous associations between aspects of cognition and measures of physical performance in PwMS [10–15]. These associations impelled recent interest in the possibility of enhancing cognition by training and improving physical performance and vice versa [6, 16]. There is preliminary evidence of improved processing speed, learning, memory and executive functions in PwMS after exercise training [6]. Literature on combined cognitive-motor interventions is scarce. A few studies have also found promising results in walking performance under dual-task conditions after dual-task training [17–19]. Two studies on combined cognitive-motor training as two separate interventions found that adding a cognitive treatment to a motor treatment improved cognitive, emotional [20, 21] and motor aspects [20] in PwMS. Ageing studies on combined cognitive-motor rehabilitation are more prevalent, with limited evidence for its effectiveness in improving cognition and functional status, both with and without the presence of CI [22–24]. However, more well-designed studies with active control groups and larger sample sizes, as well as data on the appropriate training characteristics and long-term effects, are needed before definite conclusions can be drawn.

Furthermore, there is emerging evidence that telemedicine and telerehabilitation in MS are beneficial, cost-effective and satisfactory for both patients and healthcare professionals [25], as well as low-level evidence for improvement of functional activities, fatigue and quality of life after telerehabilitation in PwMS [26]. In the context of the COVID-19 pandemic, telemedicine has gained momentum and is increasingly applied in daily practice in the follow-up of MS and other conditions [27–29] and could be of particular interest in the assessment and treatment of cognitive impairment [28].

We set up a randomised controlled clinical trial to assess whether a combined cognitive-motor telerehabilitation programme improves working memory compared to cognitive or motor telerehabilitation only in PwMS in patients with impaired working memory. Furthermore, we will assess the effect on walking performance and identify mechanisms of improvement and predictors of treatment response.

## Methods

This protocol was constructed using the SPIRIT reporting guidelines ([30], see attachment). Based on these guidelines, the following diagram was constructed:

**Table Taba:** 

	Study period							
	Enrolment	Allocation	Intervention		Follow-up			Close-out
**Timepoint**	***-T***_***1***_	**T0**	***T***_***1***_ ***= week 1***	***T***_***2***_ ***= week 12***	***T***_***3***_ ***= week 13***	***T4 = week 24***	***T***_***5***_ ***= week 64***	***T***_***6***_ ***= week 65***
**Enrolment**								
**Eligibility screen**	X							
**Informed consent**	X							
***Allocation***		X						
**Intervention preparation**		X						
**Interventions**								
***Cognitive-motor training***								
***Cognitive training***								
***Motor training***								
**Assessments**								
***Patient characteristics***	X	X						
***Neuropsychological /physical tests***	X	X			X	X	X	
***EEG***		X			X			
***MRI***		X			X	X		

### Trial design

CoMoTeMS (Cognitive-Motor Telerehabilitation in Multiple Sclerosis) is a two-centre, randomised, controlled, parallel-group and blinded clinical trial, consisting of one intervention group and two active control groups. Recruitment will start in July 2022 in the Universitair Ziekenhuis Brussel (academic hospital) and the National Multiple Sclerosis Center Melsbroek (specialist hospital). In total, 90 patients with clinically definite multiple sclerosis (based on the revised McDonald criteria 2017 [31]) will be randomised to receive either combined cognitive-motor training, cognitive training or motor training, stratified by age, sex, education and baseline activity level and cognition. This study was approved by the ethics committees of the Universitair Ziekenhuis Brussel (B.U.N. 1432022000107) and the National Multiple Sclerosis Center Melsbroek and is registered at ClinicalTrials.gov (NCT05355389, 2 May 2022). The study will be conducted in accordance with the Declaration of Helsinki, the guidelines of the International Conference on Harmonization of Good Clinical Practice (ICH-GCP) and the applicable Belgian legislation. All participants are required to give written informed consent before inclusion.

### Participants

Dutch- and/or French-speaking patients with MS will be recruited at the Universitair Ziekenhuis Brussel and the National Multiple Sclerosis Center Melsbroek, as well as through an advertisement printed in the Flanders MS society magazine and published on social media. The inclusion criteria for participation are clinically definite multiple sclerosis (revised McDonald criteria 2017, any disease course), Expanded Disability Status Scale (EDSS) [32] below 6.0, digit span backwards *z*-score between [−3 and −0.5] standard deviations below the median of the normative values [33, 34], age between 18 and 65 and ability to safely perform the motor rehabilitation programme in the home situation (assessed by a rehabilitation physician and/or occupational or physiotherapist). Exclusion criteria are participation to a cognitive rehabilitation programme within 6 months before inclusion, inpatient multidisciplinary rehabilitation programme within 3 months before inclusion or planned inpatient rehabilitation programme during trial, start of or switch in immunomodulatory treatment within 3 months prior to inclusion, less than 1 month post-exacerbation, major psychiatric or medical disorder that could influence cognitive functions, combined vision with optimal correction below 0.6 on Snellen Visual Acuity Test and the patient being unable or unwilling to undergo electroencephalography (EEG) or magnetic resonance imaging (MRI). Patients following physiotherapy at home or an outpatient multidisciplinary rehabilitation programme will not be excluded, but will be asked to postpone significant changes in intensity and content until after the trial. Furthermore, we will ask the patients to postpone inpatient multidisciplinary rehabilitation programmes from the start of the training until after the last MRI at 3 months post-training, i.e. a total period of 6 months.

### Intake and intervention

Eligibility for participation is determined at a screening visit after written consent, at which point a digit span backwards and an assessment of vision using the Snellen Visual Acuity test are performed. From patients who are eligible for participation, data on age, sex, disease type, course and duration, EDSS score, time since last relapse, medication, level of education, living situation and additional physiotherapy/rehabilitation will be collected. Furthermore, they will be randomised 1:1 to receive either combined cognitive-motor training, cognitive training or motor training, stratified by age, sex, education, baseline activity level and cognition (through minimisation of the intercentroid distances in a five-dimensional space). Each group will receive 90 min of training per week for 12 weeks. This duration and frequency are based on a systematic review on cognitive-motor rehabilitation in the elderly, which recommends a training scheme of 1 to 3 h weekly for 12 to 16 weeks [23]. Furthermore, clinical and neuroimaging assessments will be planned before and after the training programme, at 24 weeks and at 64 weeks (see Fig. 1). Neuropsychological and physical testing and EEG will take place 1 week before the start and 1 week after completion of the training. MRI measurements will be carried out in a time window of 2 weeks before and after the training.

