### Sample size

We calculated the minimal sample size with G*Power [61], using an ANOVA design (repeated measures, within-between interaction) with a power of 95% and an alpha error rate of 5%. Under the assumption of a large effect size (*f* = 0.40, based on the change in digit span backwards score after cognitive training [62]) and moderate correlation between the pre- and post-training measurements (*r* = 0.50), the required sample size is 30. Under the less favourable assumption of a medium effect size (*f* = 0.25) and a small correlation among repeated measurements (*r* = 0.30), the required total sample size is 90. In this study, we chose a total sample size of 90, with 30 subjects in each group.

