### Blinding and statistical methods

The study will be blinded: patients will not be made aware of the rationale and predictions of the study (pseudo-blinding). The randomisation procedure and the teleconsultations will be carried out and communicated to participants by a trained MS nurse, while the baseline and follow-up testing and analyses are carried out by an investigator who is blinded to the treatment allocation of the patients. Unblinding will only be done in the unlikely case of serious adverse events.

Differences between the different treatment groups in the clinical endpoints compared to baseline will be assessed with a one-sided ANOVA repeated measures test with a within-between interaction. A type I error probability of 0.05 will be used for the main effects and interaction effects. We will correct for multiple comparisons in the post hoc analyses via a family-wise error rate. Per-protocol analyses will be performed, and to correct for missing data, analyses will be repeated using the last observation carried forward method. In case of dropout before the second follow-up testing at 24 weeks, the differences in clinical endpoints at week 12 compared to baseline will still be assessed.

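### Allocation is minimised on five factors but the stated repeated-measures ANOVA adjusts for none of them, so the primary test is conservative, by an amount that depends on an unnamed cognition measure

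*Protocol article*

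**What the plan says.** Trial design and Intake and intervention (Protocol article) both list age, sex, education, baseline activity level and cognition as the balancing factors. The second section adds how this is done: the three-arm allocation is "stratified by age, sex, education, baseline activity level and cognition (through minimisation of the intercentroid distances in a five-dimensional space"). Neither section says which test supplies the cognition value or when it is taken. The only cognitive test that Intake and intervention names before randomisation is at the screening visit, "at which point a digit span backwards and an assessment of vision using the Snellen Visual Acuity test are performed". The schedule table marks neuropsychological testing at both the enrolment column and T0.

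Blinding and statistical methods names the analysis as a "one-sided ANOVA repeated measures test with a within-between interaction" and sets the error level separately: "A type I error probability of 0.05 will be used for the main effects and interaction effects". No covariate or allocation factor is mentioned. Sample size uses the same unadjusted design, with planning correlations of 0.50 and 0.30 between repeated measurements. The registration table gives the primary outcome as the change in digit span backwards from before to after treatment, so two time points.

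**The concern.** When allocation forces the arms to agree on a prognostic factor, that factor no longer contributes to chance differences between arms. An analysis that omits the factor still counts its variance as error. The estimated standard error then exceeds the true one, p-values are too large and intervals too wide.

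Having the baseline score as one of the repeated measures does not cure this. With two time points the group-by-time interaction is a one-way ANOVA on change, and change remains negatively correlated with baseline whenever r is below 1. If arms are balanced on baseline, a predictable share of the variance in change is therefore left in the error term.

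At stake are the calibration of the primary test and the precision that the minimisation could deliver. Both comparators are active, and the combined arm trains for half the weekly time on each component, so a difference smaller than the planned f = 0.25 is plausible. That is where lost precision matters.

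**Working it through.** **Inputs.** From the Protocol article: N = 90 in three equal groups, alpha 0.05, f = 0.25 with r = 0.30 and f = 0.40 with r = 0.50 (Sample size); two time points for the primary outcome (registration table). Assumptions: normal outcomes with equal variance at both times and, in steps 2, 3 and 5, a cognition factor that is the same baseline digit span used in the change score.

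**1. The plan's own figure.** For the within-between interaction with k = 3 groups and m = 2 times, lambda = f² × N × m / (1 − r), on (k − 1)(m − 1) = 2 and (N − k)(m − 1) = 87 df.
- f = 0.25, r = 0.30, N = 90: lambda = 0.0625 × 90 × 2 / 0.70 = 16.07; power 95.1%. The stated 90 reproduces.
- f = 0.40, r = 0.50: the minimum is 28, rounded up to 30 for three equal groups. The stated 30 reproduces.

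**2. Share of change explained by baseline.** R² = (1 − r)/2.
- r = 0.30: R² = 0.35. Overstatement of the SE under perfect balance = 1/√0.65 = 1.24, or 24%.
- r = 0.50: R² = 0.25. Overstatement = 1/√0.75 = 1.15, or 15%.

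**3. True size of the nominal 5% test under perfect balance.** Size ≈ P(F(2,87) > Fcrit/(1 − R²)), with Fcrit = 3.10.
- r = 0.30: 3.10/0.65 = 4.77, size 1.1%.
- r = 0.50: 3.10/0.75 = 4.14, size 1.9%.

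**4. Simulation.** Sequential minimisation of centroid distances in five dimensions, N = 90, 4,000 trials per setting. Further assumptions: 70% women, equal standardised weights, 0-20% random element.

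| Setting | Size of unadjusted test |
|---|---|
| Simple randomisation (control) | about 5% |
| Minimised on baseline digit span, r = 0.30 | 0.9-1.5% |
| Same, r = 0.50 | 2.1-2.2% |
| Same, r = 0.70 | about 3% (1.4-1.6% if the other factors are prognostic) |
| Cognition is another test, correlated 0.3-0.5 with digit span | 3.8-4.7% |

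Adjusting for the five factors brings the size back to about 5%.

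Three variants were checked separately:
- Cognition taken from a separate screening digit span: 4.7-5.6%. If all occasions correlate equally at r, as the sample-size model implies, the screening score has covariance r − r = 0 with the later change, so balancing on it removes nothing from the change score. If screening and baseline correlate more strongly (assumed 0.5-0.7), the size is 3.5-5.0%.
- All four visits in the ANOVA, balanced on baseline digit span: 2.7-2.8%.
- A one-sided 5% pairwise contrast, balanced on baseline digit span: 2.1% (r = 0.30) or 2.9% (r = 0.50).

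**5. Power under perfect balance, r = 0.30.** The noncentrality becomes lambda/0.65. The unadjusted test must exceed 4.77 on the rescaled F; the adjusted test uses its own 5% critical value on 2 and 87 − 5 = 82 df, with only baseline assumed prognostic.

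| f | lambda | lambda/0.65 | Unadjusted | Adjusted |
|---|---|---|---|---|
| 0.25 | 16.07 | 24.73 | 97.5% | 99.5% |
| 0.20 | 10.29 | 15.82 | 84% | 95% |
| 0.15 | 5.79 | 8.90 | 53% | 75% |

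**The case against.** **The size depends on something the article does not state.** A reader might infer that the primary test simply runs at 1-2%. The documents do not support that without a condition. They say only cognition, and the sole pre-randomisation test named is the screening digit span, which may be a different measurement from the T0 baseline. On that reading the test can be close to its nominal level. This objection stands and limits the size claimed here.

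**The consequence is mild.** A reader might also infer that error control fails or that the trial is underpowered. Neither follows: the error is conservative, and at f = 0.25 the unadjusted test has about 97.5% power, above the planned 95%. Nor is the balance wasted, since it still reduces the true variance of the estimate. This stands too.

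**Covariates may be in an unseen analysis plan.** They may, and an article need not list every model term. But this article does name the primary test, gives it no covariates and sizes the trial on the same unadjusted form. The mismatch with its own allocation method can be seen in the text, so the objection lowers the weight of the point without removing it.

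**Centre.** The trial "is a two-centre, randomised, controlled, parallel-group and blinded clinical trial", so a reader might want centre added on the same grounds. The argument does not reach it: centre is not a listed minimisation factor, so no balance is forced on it, and nothing in the documents shows a centre effect.

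**Conclusion.** The point holds in direction and is conditional in size. The stated analysis does not match the stated allocation, and the test is conservative to the extent that the balanced factors predict change. The 1-2% figure applies to the two-time-point interaction test at the protocol's own r = 0.30-0.50, and only if the minimised cognition score is the baseline digit span used in the change score. Otherwise the size ranges up to about the nominal 5%. The damage is to precision and calibration, not to protection against false positives, and it grows as the true effect falls below the planned one. This is a change that should be made, not a flaw that invalidates the design.

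**What to change.** State which cognitive measure enters the minimisation and at which time point. Make the primary model an ANCOVA, or an equivalent mixed model, of post-treatment digit span backwards on group, adjusted for baseline digit span and the other minimisation factors: age, sex, education and baseline GLTEQ activity.

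The cost is a sentence or two and about five of the 87 error degrees of freedom. All these variables are already collected, and the sample size need not change. Under the stated planning assumptions, power rises.

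### Recruiting centre and ongoing physiotherapy or outpatient rehabilitation are known before allocation but are not among the five minimisation factors, and no covariate is named for the ANOVA: a minor weakness that is cheap to repair

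*Protocol article*

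**What the plan says.** The Trial design section describes a "two-centre, randomised, controlled, parallel-group and blinded clinical trial" that recruits at an academic hospital and at a specialist MS hospital. Under Participants, "Patients following physiotherapy at home or an outpatient multidisciplinary rehabilitation programme will not be excluded"; these patients "will be asked to postpone significant changes in intensity and content until after the trial". Intake and intervention lists the data gathered from eligible patients, and the list ends with "medication, level of education, living situation and additional physiotherapy/rehabilitation will be collected". Both hospital and rehabilitation status are therefore baseline facts.

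The same section gives the allocation rule: 1:1 to three arms, "stratified by age, sex, education, baseline activity level and cognition (through minimisation of the intercentroid distances in a five-dimensional space". Trial design repeats the same five factors. The count of dimensions shows that the list is complete as stated.

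Blinding and statistical methods specifies a "one-sided ANOVA repeated measures test with a within-between interaction" for the clinical endpoints. It names no covariate, and it does not say that the analysis will be unadjusted.

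**The concern.** The two hospitals differ in type and may draw different patients. Outside physiotherapy may overlap with the motor component under test: a cognitive-only patient who also attends physiotherapy receives some background motor work. The request to keep such therapy stable limits change within a patient, but it does not spread users evenly over the arms.

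At 30 per arm, chance alone can leave a noticeable difference in either factor. If the factor is related to how much digit span backwards changes over 12 weeks, the combined-versus-single contrasts carry part of that difference, and variance that the factor could explain stays in the error term. At stake are a little precision and the credibility of the result after an unlucky allocation.

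**Working it through.** **1. The plan's own figure.** Inputs from Sample size: three groups, f = 0.25, r = 0.30, alpha 0.05, power 95%, N = 90. Taking two measurements (pre and post), the within-between interaction has λ = f²·N·m/(1 − r) = 0.0625 × 90 × 2/0.70 = 16.07, with 2 and 87 degrees of freedom. Power is 0.951, so N = 90 reproduces. The more favourable scenario (f = 0.40, r = 0.50, N = 30) gives 0.968 and also reproduces.

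**2. How often an unbalanced factor goes wrong.** The article gives no prevalence for either factor, so p is assumed. The factor is taken as yes/no and unrelated to the five minimised factors. The SD of the difference in proportions between two arms is √[2p(1 − p)/30].

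| Assumed p | SD of difference | ≥20 points, one contrast | ≥20 points, at least one of the two contrasts with the combined arm |
|---|---|---|---|
| 0.5 | 0.129 | 15% | 26% |
| 0.3 | 0.118 | 12% | 21% |
| 0.2 | 0.103 | 7% | 13% |

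These percentages count imbalances in both directions. About half of those in a single contrast favour the combined arm.

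**3. What an imbalance does.** The outcome is change, tested as group by time. If the factor shifts all of a patient's scores by the same amount, it cancels. If it shifts the change by e (in SD of change), the contrast moves by e × imbalance.

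- At an assumed e = 0.5 and an imbalance of 0.20, the shift is 0.10 SD. The standard error of a 30 v 30 contrast is √(2/30) = 0.258 SD, so the shift is 0.39 standard errors.
- Given that imbalance in favour of the combined arm, an uncorrected one-sided 5% contrast would reject a true null with probability P(Z > 1.645 − 0.39) = 10.4%. Given the mirror imbalance, it would do so with probability P(Z > 1.645 + 0.39) = 2.1%.
- At e = 0.3 the shift is 0.06 SD and the first figure is 7.9%.
- In test points, assumed effects of 0.25 to 1.0 point on change give shifts of 0.05 to 0.20 point. The article treats one point as clinically significant.

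**4. Average error rate.** In simulations of the three-arm F-test on change scores at p = 0.5, leaving the factor out gave rejection rates under the null of 0.049 to 0.052 for factor effects from 0.25 to 1 SD. That is nominal.

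**5. Precision.** With p = 0.5 the factor explains R² = e²p(1 − p)/[1 + e²p(1 − p)] of the variance in change: 0.0225/1.0225 = 2.2% at e = 0.3 and 0.0625/1.0625 = 5.9% at e = 0.5. The latter is worth about 0.059 × 90 ≈ 5 patients. For an assumed treatment effect of 0.7 SD in the combined arm alone, λ = 30 × 0.7² × 2/3 = 9.8 with the factor in the model and 9.8/1.0625 = 9.22 without it (e = 0.5). Power is about 0.79 and 0.77 respectively.

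**6. Price of the remedy.** Two yes/no terms reduce the error degrees of freedom from 87 to 85. Under the plan's own assumptions, power stays at 0.951 if they explain nothing. It becomes 0.955, 0.960 or 0.969 if they explain 2, 5 or 10% of the variance in change.

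**The case against.** The strongest objection is that the analysis side rests on silence. A journal article commonly leaves covariates to the full protocol or analysis plan, so the article cannot show that the comparison will be unadjusted. That stands. What the article does fix is the list of minimisation factors.

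The documents also make a large effect on change less likely. Training is done at home with the same software and watch whichever hospital recruits. Background therapy is to be kept stable. Activity in the cognitive-only arm is monitored, and baseline activity level, already a minimisation factor, may partly balance concurrent physiotherapy. These points reduce the probable size, but none of them balances centre.

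A reader might infer that any imbalance biases the training contrasts directly, or that the true type I error exceeds 0.05. The documents support neither. The group-by-time test removes constant differences in level, randomisation keeps the average error nominal, and the 10.4% above is conditional on one adverse allocation. It also uses an uncorrected cut-off, whereas the article promises family-wise correction for post hoc comparisons.

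Finally, the choice of balancing factors is partly a matter of judgement, and other recorded variables could be proposed on similar grounds. These two have the better claim: one is the site structure of the trial, and the other is a permitted co-intervention that may resemble the motor training being tested.

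**Conclusion.** The point holds as a minor design weakness. Two relevant factors, both known before allocation, lie outside the stated minimisation, and the article names no adjustment for them. Under the assumed prevalences of 30 to 50%, an imbalance of 20 points or more with at least one comparator occurs in about one trial in four or five. Its consequence depends on an assumed effect on change for which the documents give no estimate: at 0.5 SD, a shift of 0.10 SD and about two to three percentage points of power. If neither factor affects 12-week change, nothing is lost. The stated alpha is not in error, and the sample size reproduces.

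**What to change.** - **Allocation.** For patients still to be randomised, add centre as a sixth dimension of the minimisation and document the date of the change. This needs an amendment and a change to the allocation algorithm, and it slightly loosens balance on the other five factors.
- **Analysis.** Prespecify centre (two levels) and baseline physiotherapy or outpatient rehabilitation (yes/no), either as terms interacting with time in the repeated-measures ANOVA or as covariates in a model of change. Entered only as main effects in the repeated-measures ANOVA, they would not adjust the group-by-time interaction. Fix this before any unblinded look at the data, so that covariates are not chosen after an imbalance is seen. If the analysis plan already does this, a sentence under Blinding and statistical methods saying so is enough.

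The analysis change uses two of 87 degrees of freedom. It needs no new data, visits or patients, because rehabilitation status is already collected at intake and the recruiting hospital is known.
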